| outcomes | Outcome measures | Primary outcome       | Change in ADAS-Cog scores before and 8 weeks after stimulation in the rTMS group.                                                                                                                                                                                                                                                                                                                                                                                                                                                                                                                                                                                                                                                                                                                                                                                                                                                                                                                                                                                                                                                                                                                             |
|          |                  | Secondary outcome     | 
<Comparison Before and After rTMS Stimulation>
 
The change in scores at baseline, 4 weeks, and 8 weeks based on neuropsychological assessments (K-MMSE, K-MoCA, CDR-SOB, ADAS-Cog/COWAT, Stroop, TMT, RVP, SWM, PRM) in the rTMS stimulation group. The change in total scores derived from K-GDS short form between baseline, 4 weeks after stimulation, and 8 weeks after stimulation.
 
The change in S-IADL scores between baseline, 4 weeks after stimulation, and 8 weeks after stimulation.
 
Functional network changes in resting fMRI at 4 weeks after stimulation.
 
Change in FA values in DTI analysis at 4 weeks after stimulation.
 
<Comparison between rTMS and Sham Groups>
 
 
- The changes in scores of K-MMSE, K-MoCA, CDR, ADAS-Cog, COWAT, Stroop, TMT/PRM, RVP, and SWM between the rTMS treatment group and the sham group are compared.
 
- The changes in FA values in MRI DTI analysis between the rTMS treatment group and the sham group are compared.
 
- Qualitative comparison of functional network changes in fMRI between the rTMS treatment group and the sham
 
 |

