#### 1) Primary objective

- Comparison Before and After Stimulation in the rTMS Group:

-The change in ADAS-Cog scores at the 8-week follow-up after 4 weeks of repetitive Transcranial Magnetic Stimulation (rTMS) applied to the parietal region was measured.

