#### ●Comparison Between the Experimental Group and the Control Group (Sham Group):

- A comparison of changes in K-MMSE, K-MoCA, CDR, ADAS-Cog, COWAT, Stroop, TMT/PRM, RVP, and SWM scores between the rTMS stimulation group and the sham group.
- A comparison of changes in MRI DTI analysis, specifically FA values, between the rTMS stimulation group and the sham group.
- A qualitative comparison of functional network changes in fMRI between the rTMS stimulation group and the sham group, focusing on assessing alterations in connectivity patterns.

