## 9. Methods

### A. Clinical Trial Design and Randomized Allocation

#### 1) Primary Outcome Measure

- 1) Study Design: Single-arm design
- 2) Allocation: Random assignment
- 3) After 4 weeks of rTMS stimulation, changes in K-MMSE, K-MoCA, CDR-SOB, ADAS-Cog, COWAT, Stroop, TMT, RVP, SWM, PRM scores will be compared at an 8-week follow-up.
- 4) masking: Blinded assessment by evaluators

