#### 2) Secondary Outcome Measure

- 1) Study Design: Single-arm design
- 2) Allocation: Random assignment
- 3) -Compare changes in K-GDS short form and S-IADL scores between baseline, 4 weeks after rTMS stimulation, and 8 weeks after.  
-Compare changes in K-MMSE, K-MoCA, CDR-SOB, ADAS-Cog, COWAT, Stroop, TMT, RVP, SWM, PRM scores between baseline and after 4 weeks of rTMS stimulation.  
-Compare FA values in DTI analysis at 4 weeks after rTMS stimulation.  
-Examine functional network changes in resting-state fMRI at 4 weeks after rTMS stimulation.
- 4) masking: Blinded assessment by evaluators

- 1) Study Design: Parallel design
- 2) Allocation: Random assignment
- 3) Intervention Group: rTMS application group  
Control Group: Sham group (sham coil emits sound only, no rTMS stimulation)
- 4) -Compare K-MMSE, K-MoCA, CDR, ADAS-Cog, COWAT, Stroop, TMT, RVP, SWM, PRM scores between intervention and control groups after 4 weeks.  
-Compare FA values in DTI analysis between intervention and control groups at 4 weeks after.  
-Examine functional network changes in resting-state fMRI between intervention and control groups at 4 weeks after.
- 5) masking: Blinded assessment by evaluators

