## 10. Observation Items and Observation Methods

### Clinical trial schedule (for rTMS group)

| Visit No                                                            |                                        | VISIT 1~3                             |          | VISIT 4~
VISIT 23             | VISIT 24~25 | VISIT 26  |
|---------------------------------------------------------------------|----------------------------------------|---------------------------------------|----------|----------------------------------|-------------|-----------|
| Visit schedule                                         |                                        | Screening                             | baseline | rTMS application                 | Follow up   | Follow up |
|                                                                     |                                        |                                       |          | 20 session for 4 weeks (Mon~Fri) | 4 week      | 8 week    |
| Visit window                                                        |                                        |                                       |          |                                  | ± 7 day     | ± 7 day   |
| Clinical trial explanation and informed consent preparation         |                                        | ●                                     | (●)      |                                  |             |           |
| Eligibility determination (inclusion /exclusion criteria)           |                                        | ●                                     | (●)      |                                  |             |           |
| Demographic data                                       |                                        | ●                                     | (●)      |                                  |             |           |
| Vital sign                                             |                                        | ●                                     | (●)      |                                  | ●           | ●         |
| history taking                                         |                                        | ●                                     | (●)      |                                  |             |           |

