## 13. Outcome Measure, Statistical Analysis, and Interpretation

### 13.1. Outcome Measure

#### A. Primary Outcome Measure

Change in ADAS-Cog test scores after 8 weeks of rTMS stimulation and the difference in change scores at the 8-week time point.

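### The primary result is defined as a before-after ADAS-Cog change within the rTMS arm, although a randomised sham arm exists, and the protocol contradicts itself on the primary contrast

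*Protocol*

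**What the plan says.** Three places in the Protocol define the primary result within one arm:

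- The synopsis gives the primary outcome as "Change in ADAS-Cog scores before and 8 weeks after stimulation in the rTMS group".
- Section 6.A.1 (primary objective) is headed "Comparison Before and After Stimulation in the rTMS Group".
- Section 9.A.1 describes the primary outcome under "Study Design: Single-arm design", with random assignment on the next line. It lists ten instruments there, where the synopsis names ADAS-Cog alone.

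The sham arm is real and concurrent: sections 7.D and 9.B set 16 participants for rTMS and 16 for sham. Its comparison with rTMS is secondary. Section 6.A.2 includes "A comparison of changes in K-MMSE, K-MoCA, CDR, ADAS-Cog, COWAT, Stroop, TMT/PRM, RVP, and SWM scores between the rTMS stimulation group and the sham group". Section 9.A.2 gives that part the label "Study Design: Parallel design" and compares "scores between intervention and control groups after 4 weeks".

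Other places point towards a group comparison:

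- Section 13.1.A adds to the primary outcome "and the difference in change scores at the 8-week time point", without naming what is compared.
- Section 7.A states a between-group hypothesis beside the before-after one.
- Section 13.2 names a linear mixed model with group and time among its fixed effects, but no primary contrast.
- The design row of the synopsis ticks both the single-arm and the parallel box.

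**The concern.** Section 6.A says the trial aims to demonstrate that rTMS improves memory and cognition. A before-after change in treated participants contains everything that happened between the two assessments, not only the effect of the device. Three components are plausible here:

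- **Practice.** ADAS-Cog is repeated at baseline, 4 weeks and 8 weeks.
- **Attention and expectation.** Participants attend 20 stimulation sessions, and section 9.D concedes that participant blinding may be incomplete.
- **Natural decline.** The section 10 footnotes allow baseline cognitive results up to 6 months old at first stimulation.

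The first two favour rTMS and the third works against it, so an inert device could look effective and a useful one could look inert. The sham arm is there to remove the part common to both arms, but three of the four definitions of the primary result do not use it. Section 7.D also says the study will inform the size of a confirmatory trial, so a within-arm change would carry its non-specific part into that calculation.

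**Working it through.** **1. The plan's own figure.** Section 7.D gives 16 per arm by reference to earlier studies of 14 and 16 patients. It states no alpha, power, effect size or SD, so the number cannot be reproduced.

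**2. Definitions side by side.**

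| Place | Primary contrast |
|---|---|
| Synopsis | rTMS arm, before-after, 8 weeks |
| 6.A.1 | rTMS arm, before-after, 8 weeks |
| 9.A.1 | single-arm, 8 weeks, ten instruments |
| 13.1.A | change after rTMS, plus an 8-week difference in change, groups not named |
| 13.2 | mixed model with group and time, no primary contrast named |

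Section 13.1.B, written in parallel for the secondary outcomes, does say that the difference is between the two groups. If 13.1.A means the same, it contradicts the first three rows. If it does not, the primary result has no control. Either reading needs correction.

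**3. What an uncontrolled change can produce.** These inputs are assumptions and none is in the Protocol: no true rTMS effect; SD of ADAS-Cog change 4 or 5 points; non-specific improvement (a fall in score) of 1 to 2 points; one-sample t-test on change, n = 16, two-sided 5%.

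Noncentrality = (shift / SD) × √16. Critical value t(0.975, 15) = 2.131. The probability of a significant result in favour of rTMS is the upper tail of the noncentral t beyond 2.131:

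| Shift | SD 5 | SD 4 |
|---|---|---|
| 1.0 | 0.20 × 4 = 0.8 → 11.3% | 0.25 × 4 = 1.0 → 15.3% |
| 1.5 | 0.30 × 4 = 1.2 → 20.2% | 0.375 × 4 = 1.5 → 28.9% |
| 2.0 | 0.40 × 4 = 1.6 → 32.2% | 0.50 × 4 = 2.0 → 46.5% (0.4648) |

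The nominal rate in that direction is 2.5%.

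**4. The opposite direction.** Suppose a true effect of 0.75 SD, which the within-arm test would detect with 80% probability. A natural decline of 0.25 SD leaves a net 0.50 SD and 46%. A decline of 0.5 SD leaves a net 0.25 SD and 15%.

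**5. The between-arm test.** With 16 per arm and drift of 0 to 0.75 SD shared by both arms, the two-sided rejection rate with no rTMS effect was 5.0% to 5.2% in 40,000 simulated trials per setting.

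**6. Cost in precision, in SDs of change.**

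- 95% CI half-width within one arm: 2.131 / √16 = 0.53.
- 95% CI half-width between arms: 2.042 × √(2/16) = 0.72.
- Effect detectable with 80% power: 0.75 within one arm, 1.02 between arms.
- Between-arm power: 28% at 0.5 SD, 54% at 0.75 SD, 78% at 1.0 SD.

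**The case against.** The strongest reply is that the Protocol does not abandon the comparison. Section 7.A states a between-group hypothesis, 13.1.A mentions an 8-week difference in change, and 13.2 describes both arms and names a model with group in it. No paired or single-arm test is specified anywhere. This stands: a reader might infer that the randomisation is simply discarded, and the documents do not support that. They support an uncontrolled primary definition in three places and a contradiction with others.

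Four further inferences would go too far:

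- **That sham participants are not followed to 8 weeks.** The schedule is headed "Clinical trial schedule (for rTMS group", but its rows include randomisation and device application for both groups. The heading looks like a slip.
- **That the sham comparison exists only at 4 weeks.** Only 9.A.2 is so limited. Section 13.1.B gives neuropsychological change at 4 and 8 weeks and the difference between groups.
- **That ADAS-Cog is always given three times within 8 weeks.** Baseline results may be up to 6 months old, which weakens the practice argument and strengthens the one about decline.
- **That regression to the mean inflates the result directly.** Selection for low memory scores uses SVLT or RCFT delayed recall, not ADAS-Cog, so the route is at most indirect.

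The trial is also called exploratory, and no significance criterion is set. That lowers the stakes of any single p-value, but it does not remove bias from the estimate. Finally, sham removes only what both arms share. With incomplete participant blinding, some difference in expectation may remain.

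**Conclusion.** The point holds. Followed as the synopsis and sections 6.A.1 and 9.A.1 are written, the headline result cannot be attributed to rTMS, and section 13 does not state clearly enough what replaces it. This should be corrected before analysis.

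The contradiction is read directly from the text and rests on no assumption. The 11% to 46% range does rest on assumptions: the drift, the SD, the alpha and the t-test are not in the Protocol. The range shows the mechanism and does not estimate the error in this trial. The direction of any actual bias is unknown.

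**What to change.** State one primary result in the synopsis, 6.A.1, 9.A.1 and 13.1.A: the rTMS-minus-sham difference in ADAS-Cog change from baseline to the 8-week visit, in all randomised participants. In 13.2, name the group-by-time contrast at week 8 of the mixed model as its estimator, reported with a 95% CI.

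Then align the rest:

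- Remove the single-arm labels from the synopsis design row, 9.A.1 and 9.A.2.
- Add the 8-week sham comparison to 9.A.2, to agree with 13.1.B.
- Keep the within-rTMS change as a secondary or descriptive result.
- Reconcile the all-randomised population with 12.2.2, which removes some withdrawn participants from the study population.

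No new data are needed, because both arms are already randomised and treated and 13.1.B already calls for 8-week group differences. It is nonetheless a change of primary outcome and needs an amendment. The cost is precision: the detectable effect rises from about 0.75 to 1.02 SD of change and the CI half-width from 0.53 to 0.72 SD. Since no power is stated, no stated claim is lost. Adjustment for baseline ADAS-Cog could recover some of the precision.

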## **1. Clinical Trial Title**

The effects of transcranial magnetic stimulation (ALTMS) on cognition in the patients with Alzheimer's disease: A single centered, randomized, evaluator-blinded, exploratory clinical trial

## 6. Objective and Background

### A. Objectives

This clinical trial aims to demonstrate the improvement of memory and cognitive function using transcranial magnetic stimulation applied to the parietal region in patients with Alzheimer's disease.

#### 1) Primary objective

- Comparison Before and After Stimulation in the rTMS Group:

-The change in ADAS-Cog scores at the 8-week follow-up after 4 weeks of repetitive Transcranial Magnetic Stimulation (rTMS) applied to the parietal region was measured.

#### 2) Secondary objective

- Comparison Before and After Stimulation in the rTMS Group:

-The change in CANTAB PRM, RVP, and SWM scores at 4 and 8 weeks after 4 weeks of repetitive Transcranial Magnetic Stimulation (rTMS) applied to the parietal region was measured to assess cognitive function changes.

-The change in K-MMSE, K-MoCA, CDR-SOB, COWAT, Stroop, and TMT scores at 4 and 8 weeks after 4 weeks of rTMS treatment was measured and compared with baseline scores to assess cognitive function changes.

-The change in ADAS-Cog scores at 4 weeks after 4 weeks of rTMS treatment was measured and compared with baseline scores to assess cognitive function changes.

-The change in K-GDS short form scores at 4 and 8 weeks after using rTMS was measured and compared with baseline scores to assess emotional changes.

-The change in S-IADL scores at 4 and 8 weeks after using rTMS was measured and compared with baseline scores to assess changes in daily life functions.

-The change in FA (fractional anisotropy) values through diffusion tensor image (DTI) analysis **at 4**

weeks after using rTMS was measured and compared with baseline to assess white matter microstructure changes.

-The qualitative assessment of functional network changes in resting-state fMRI at 4 weeks after using rTMS was conducted by comparing with baseline, involving correlation, coherence, and spatial grouping based on temporal similarities in BOLD images to analyze simultaneously activated brain regions.

#### ●Comparison Between the Experimental Group and the Control Group (Sham Group):

- A comparison of changes in K-MMSE, K-MoCA, CDR, ADAS-Cog, COWAT, Stroop, TMT/PRM, RVP, and SWM scores between the rTMS stimulation group and the sham group.
- A comparison of changes in MRI DTI analysis, specifically FA values, between the rTMS stimulation group and the sham group.
- A qualitative comparison of functional network changes in fMRI between the rTMS stimulation group and the sham group, focusing on assessing alterations in connectivity patterns.

## **B. Backgrounds**

In South Korea, according to data from the Ministry of Health and Welfare in 2009, the elderly population aged 75 or above was already reported as 7.2% in the year 2000, marking the entry into an "aging society". By 2018, this percentage had increased to 14.3%, indicating the transition to an "aged society". It is predicted that by around 2030, similar to advanced countries like the United States and Europe, the elderly population will surpass 23% of the total population, entering an "ultra-aged society". The prevalence of dementia increases with age, doubling approximately every 5 years after the age of 65. Thus, while the prevalence is around 2-3% in the age group of 65-69, it geometrically escalates to about 4-6% in the 70-74 age group, 8-12% in the 75-80 age group, and over 20% in those aged 80 and above.

The rapid increase in the elderly population is closely related to a surge in dementia patients, resulting in social and economic issues that have now become significant national concerns. Two common causes of dementia are vascular dementia and Alzheimer's disease. Vascular dementia is

linked to risk factors such as brain infarcts, hypertension, and hypercholesterolemia, which can be managed to prevent progression. However, Alzheimer's disease, in contrast, lacks medication or non-pharmacological treatment to effectively improve cognitive functions or halt its progression. Notable medications include cholinesterase inhibitors or memantine (N-methyl-D-aspartate receptor antagonists).

Transcranial Magnetic Stimulation (TMS) is a non-pharmacological treatment method that involves stimulating the scalp to enhance brain activity with safety and minimal side effects. It has long been recognized for effectively reducing symptoms of conditions like depression, anxiety, and addiction. In recent years, TMS has gained attention for its potential to enhance brain activity in normal aging individuals, with some reports suggesting temporary improvements in language abilities after stimulation in the frontal lobe of Alzheimer's patients. However, research on improving cognitive functions or preventing cognitive impairment in Alzheimer's disease patients through TMS is limited.

Among these methods, Repetitive Transcranial Magnetic Stimulation (rTMS) involves delivering repeated stimulations of the same intensity and frequency to a specific brain area. This procedure is known to modulate cortical excitability over a certain period. The pattern of change in cortical excitability is influenced by factors such as the intensity, frequency, and total number of stimulations. Frequency is particularly crucial, with studies indicating that 1Hz low-frequency stimulation generally inhibits cortical excitability, while frequencies above 5Hz increase it. Long-term depression and long-term potentiation are involved in excitability inhibition and enhancement, respectively, through these processes, inducing neural plasticity. Prior studies reporting improvements in memory primarily utilized high-frequency stimulation at 20Hz.

Therefore, this study aims to investigate whether repetitive transcranial magnetic stimulation (rTMS, 20Hz) can lead to cognitive changes, including memory enhancement, in elderly individuals with Alzheimer's disease.

## **7. Inclusion Criteria, Exclusion Criteria, and Sample Size Determination**

### **A. Research Hypotheses**

#### ● Null Hypotheses:

-There will be no significant difference in cognitive abilities before and after receiving 4 weeks of rTMS stimulation.

-There will be no significant difference in cognitive abilities between the group that received 4 weeks of rTMS stimulation and the group that received sham stimulation.

#### ● Alternative Hypotheses:

-There will be a significant difference in cognitive abilities before and after receiving 4 weeks of rTMS stimulation.

-There will be a significant difference in cognitive abilities between the group that received 4 weeks of rTMS stimulation and the group that received sham stimulation.

### **B. Inclusion Criteria**

1) aged between 55 and 90 years

2) diagnosed as either mild cognitive impairment due to AD or mild AD dementia on the basis of National Institute on Aging–Alzheimer’s Association criteria, with amyloid positivity determined by PET or CSF testing

3) Objective memory impairment as indicated by at least 2 standard deviations below the age- and education-adjusted mean in verbal language test (SVLT) or Rey-copy figure test (RCFT) delayed recall tests

4)  $\geq 18$  of Mini-Mental State Examination (MMSE) score

5) no history of epilepsy

- 6) normal in electroencephalography (EEG)
- 7) no myocardial infarcts or arrhythmia in electrocardiography (ECG)
- 8) those who are literate
- 9) those who voluntarily submitted written consents.

### **C. Exclusion Criteria**

- 1) with other medical or surgical diseases that caused dementia
- 2) with serious medical conditions such as cancer, heart disease, and major surgical conditions
- 3) with severe white matter hyperintensities (WMH) on magnetic resonance image (MRI), which were defined as deep WMH  $\geq 25$  mm and periventricular WMH  $\geq 10$  mm;
- 4) who could not undergo MRI due to side effects related to contrast agents, or claustrophobia;
- 5) who have implanted medical devices that are susceptible to electronic disturbance, such as pacemaker, or detachable metallic materials (prosthetics, braces, cochlear implants etc.);
- 6) who have undergone cerebrovascular surgery, such as coiling clipping, and carotid artery stenting;
- 7) who have difficulty breathing when sitting;
- 8) who have lost consciousness for more than one hour due to causes other than general anesthesia;
- 9) who have been hospitalized with a head trauma;
- 10) who cannot read even with glasses due to reduced vision;
- 11) who have difficulty understanding conversations due to hearing impairment even with a hearing aid;
- 12) who have taken ototoxic drugs or have been exposed to loud noises
- 13) unsuitable for clinical trial participation judged by investigators

